
**Figure 2 figure2:**
[figure not shown]
Example skin marker shape and setup for the cadaver trials. (A) Circles (lines: 10 mm in length, 3 mm wide) and squares (lines: 10 mm in length, 3 mm wide) will be placed on the skin and liner, respectively. (B) Example marker placement on the skin on a scanned, translucent residual limb in the anterior-lateral view.

**Figure 3 figure3:**
[figure not shown]
Static testing of a sample cadaver marker set in the dynamic stereo x-ray system. (A) and (B) X-ray images of the residual tibia, socket, and skin markers from the inline and offset x-ray views. Note the cluster of skin (lines in the shape of a circle), liner (triangles), and socket (beads) markers and the bone edges. (C) The x-ray and computed tomography images are fused to create a 3D model with coregistration of the socket and skin markers and bone geometry.

### Optimization of the Marker Set

An iterative, heuristic approach will be used with the goal of accurately tracking all end points of each line for the skin and liner marker sets without (or minimal) occlusion while simultaneously tracking the underlying tibial movement. Notably, if there is too much overlap of the lines and tracking is not possible with the lines, additional shapes will be evaluated, and the centroid of each shape will be tracked. Cadaver trials will be sequential, and the marker set will be evaluated through tracking of each marker and performing preliminary deformation analysis after each cadaver trial. Once an acceptable marker protocol has been achieved heuristically, it will be tested on subsequent cadavers to ensure that it is robust for differing anatomies and residual limb lengths. Shorter residual limbs could potentially limit the number of markers that could be applied to the skin. As such, a minimum length may be required for skin and liner marker tracking, which would be then reflected in the inclusion and exclusion criteria.

### Deformation Analysis

The markers on the cadaver skin and the inner surface of the liner will be tracked during the simulated stance phase, and their trajectories in both the socket and tibia coordinate systems will define the motion of the skin relative to the socket and tibia, respectively. Their positions in the socket and tibia coordinate systems during the static trial will serve as their baseline positions. Visual3D (C-Motion, Inc) contains the tools to define the socket and tibia coordinate systems and track the motion of the skin and liner markers within these reference frames. Two metrics will be used to quantify skin and liner deformation. The first, shear, is defined as the change in angle between the lines painted on the skin and liner from the baseline position. The end points of the lines forming the circles and squares will be digitized, and the 3D trajectories will be used to reconstruct the 3D shape of the line at each time frame. The angles between the lines will be measured in the static pose to quantify the baseline skin shear. The change in angles will be measured during the simulated stance phase. Shear will be measured as the change in angle relative to the angle in the static position. The second, compression, will be quantified by calculating the change in distance between the lines and a neutral position. As with shear, baseline distances will be calculated from the static trial. From these values, 3D strain maps of the highest areas of deformation will be developed for both the liner and the skin.

### Validation of DSX Strain Measurements

In conjunction with the cadaver experiments, to validate the accuracy of proposed methods to measure skin deformation, a customized, mechanical testing setup (Acumen 3AT axial-torsion system, MTS Systems Corp), which can directly interface with the DSX system, will be used. This system permits mechanical testing of soft tissue to be simultaneously performed during DSX data captures (Figure 4). This setup will be used to apply displacements to cadaveric lower limb tissue (mimicking tissue deformation in the socket) to validate the measurements from the proposed DSX analysis. To perform this validation test, 5 segments of cadaveric skin and subdermal tissue will be dissected to be mechanically tested in conjunction with DSX imaging. Each tissue sample will be affixed in tension between the opposing rings of a radiolucent plastic fixture with the skin held taut between the rings using radiolucent hardware. To validate the deformation analysis, radiopaque markers used in the cadaver experiments will be painted on the tissue. A CT scan, as previously described, of each tissue sample with applied markers will be obtained before testing to model the tissue specimen and locate the markers in a 3D space. The DSX apparatus will be angled at a maximum of 30° to distinguish the markers on the horizontal surface to avoid occlusion by the metal structures of the mechanical testing system. The mechanical testing compression rings will allow translation while the center of the fixture below the sample will be open to allow the tissue to freely deform with the applied force. Both the plastic circular fixture attachment and compressive bending fixture will be fabricated from polylactic acid thermoplastic, which is radiolucent. The Acumen 3AT axial-torsion system will be used for mechanical testing with a maximum axial testing capacity of 3 kN. To remove the effects of tissue freezing, the samples will be preconditioned at 0.1 mm/s with an axial displacement loading between 0.1 and 0.5 cm, for 50 cycles, based on the results of a previous study [32]. This displacement (0.5 cm) corresponds to the minimum bone-socket displacement associated with patellar straps, sleeves, or suspension liners [11]. Following this, the displacements associated with vacuum (1.3 cm) and traditional suction (1.8 cm) for the bone-socket interface [11] will be tested for 10 cycles each in compression at a displacement rate of 1 mm/s [32]. The axial displacement, axial force, and time will be recorded with high-speed data acquisition while the tissue is simultaneously imaged by the DSX system. A digital input-output connection will be used to synchronize the 2 systems. The compressive force on the skin tissue is proportional to the distance from the origin of the bending load, and the skin strain and shear stress can thus be calculated for a given symmetric, circular geometry. The skin strain will be compared directly to the strain calculations derived from the position of the markers collected by the DSX system. To account for the asymmetry present in the skin, the geometries, boundary conditions, material properties, and the loading regimen will be simulated using finite element analysis (Ansys, Inc). This analysis will be compared to the mechanical testing results along the skin to determine the degree to which the asymmetry of the skin affects the strain measurements.

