During the cyclical loading and unloading of the residual limb during the gait cycle, the skin of the residual limb is exposed to nonphysiological stresses and strains, including excessive shear forces [24]. Although the skin is well adapted to compressive force, excessive shear force can be damaging, leading to abrasions, wounds, and ulcers [25,26]. Understanding in-socket skin strain biomechanics is critical for enhancing prosthetic socket fit, limb health, and overall comfort. However, whole-limb skin strain analysis is complicated by the heterogeneous composition of the skin and its anisotropic mechanical properties. Some investigations have used 3D digital image correlation (DIC) to create full-field deformation and strain maps of an unsupported residual limb [27]. Lin et al [28] examined skin strain in a flexed biological residual limb from an individual with transtibial limb loss and showed that the anterior patella region of the limbs exhibited predominantly tensile strains, whereas the posterior patella region exhibited predominately compressive strains. Although 3D DIC evaluations have provided critical data to help improve the mechanical interface of sockets and liners to limit relative motion and shear forces on the skin surface, these investigations only considered strain on an unloaded residual limb. Whole-limb strain fields can drastically change during dynamic, weight-bearing activities while using a prosthetic interface. Furthermore, 3D DIC and other imaging techniques are further complicated by the need for transparent biomechanical interfaces to accurately compute the strain analysis. Other techniques, such as magnetic resonance imaging and CT, can be used to evaluate in vivo strains, but they are also limited by static protocols, low resolution, motion artifacts, and shape distortion [29]. Gale et al [30] used DSX to measure residual limb skin strain and strain rate for individuals with transfemoral limb loss during gait and found that shear strain increased from proximal to distal regions of the residual limb. The proposed investigation will use time-efficient and highly accurate analytical techniques to measure in-socket residual limb skin strain for individuals with transtibial limb loss during dynamic activities.

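### The bench test's reference strain is calculated, not measured, so comparing it directly with DSX does not separate DSX error from reference-model error

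*Protocol article*

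**What the plan says.** All of this is in the Protocol article, section Validation of DSX Strain Measurements, unless another section is named.

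- **Purpose:** "to validate the accuracy of proposed methods to measure skin deformation".
- **Specimens:** "5 segments of cadaveric skin and subdermal tissue will be dissected to be mechanically tested in conjunction with DSX imaging".
- **Loading:** after preconditioning, "the displacements associated with vacuum (1.3 cm) and traditional suction (1.8 cm) for the bone-socket interface" are each applied for 10 cycles.
- **Recorded apart from DSX:** "The axial displacement, axial force, and time will be recorded with high-speed data acquisition", synchronised with the imaging. No independent strain measurement on the skin is described.
- **Reference strain:** it is derived from a relation between compressive force and distance from the bending load, so that "the skin strain and shear stress can thus be calculated for a given symmetric, circular geometry".
- **Comparison:** "The skin strain will be compared directly to the strain calculations derived from the position of the markers collected by the DSX system".
- **Asymmetry:** a simulation is planned: "To account for the asymmetry present in the skin, the geometries, boundary conditions, material properties, and the loading regimen will be simulated using finite element". Its output is then compared with the mechanical testing results, to see how much asymmetry affects the strain measurements.

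The Background section also notes that "whole-limb skin strain analysis is complicated by the heterogeneous composition of the skin and its anisotropic mechanical properties".

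**The concern.** An accuracy study needs a reference whose own error is known or small beside the error under study. Here the reference is a strain from an idealised symmetric model, and the section itself accepts that the tissue is not symmetric. If DSX and the model disagree, the cause may be marker tracking or the model. If they agree, two errors may have offset each other.

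This matters because it is the only skin-strain validation the article describes. The earlier validation cited under Data Processing is for volumetric model-based tracking, which that section applies to the tibia. The skin and liner line ends are to be digitised manually (Quantification of Skin and Liner Deformation), and Limitations expects some tracker error. Aim 1 is accurate tracking that includes tissue and liner deformation, and the study hypothesis depends on the method being highly accurate. An error figure that cannot be assigned to DSX supports those claims less well than it could.

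**Working it through.** The article states no agreement limit or error bound for the bench test, so there is no figure to reproduce. The check is a decomposition of the comparison, followed by an illustration.

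**1. What the direct comparison estimates.** For one location and frame:

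DSX strain − reference strain = (DSX strain − true strain) + (true strain − reference strain) = DSX error + model error.

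Only the sum is observed. Repetition does not split it. The plan gives 5 samples × 2 displacements × 10 cycles = 100 cycles, but a model that misdescribes a sample does so in every cycle of that sample.

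**2. What the finite element step adds as written.** It is compared with the mechanical results, which informs the model-error term. No comparison of finite element strain with DSX strain is stated, so the DSX-error term is not isolated.

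**3. Illustration of model sensitivity.** The displacements d = 1.3 and 1.8 cm are from the article. The sample radius R is not given, so 3 to 6 cm is assumed. Two symmetric shapes are compared. They are chosen for illustration and are not the plan's model.

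- Cone: mean radial strain = √(R² + d²)/R − 1
- Spherical cap: ρ = (R² + d²)/(2d); mean radial strain = ρ·asin(R/ρ)/R − 1

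Example, R = 5, d = 1.3. Cone: √(25 + 1.69)/5 − 1 = 0.033. Cap: ρ = 26.69/2.6 = 10.27, giving 0.044.

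| R (cm) | d (cm) | Cone | Cap | Difference | Difference ÷ cone |
|---|---|---|---|---|---|
| 3 | 1.3 | 0.090 | 0.121 | 0.031 | 34% |
| 3 | 1.8 | 0.166 | 0.225 | 0.059 | 36% |
| 4 | 1.3 | 0.051 | 0.069 | 0.018 | 35% |
| 4 | 1.8 | 0.097 | 0.130 | 0.033 | 34% |
| 5 | 1.3 | 0.033 | 0.044 | 0.011 | 33% |
| 5 | 1.8 | 0.063 | 0.084 | 0.021 | 33% |
| 6 | 1.3 | 0.023 | 0.031 | 0.008 | 35% |
| 6 | 1.8 | 0.044 | 0.059 | 0.015 | 34% |

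The absolute difference depends strongly on the assumed radius. The relative difference stays near one third.

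**4. Asymmetry.** Move the peak of the cone off centre by 10% of R. At R = 5 and d = 1.3, the two sides become √(4.5² + 1.3²)/4.5 − 1 = 0.041 and √(5.5² + 1.3²)/5.5 − 1 = 0.028, against 0.033 when centred.

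**5. How one result has two readings.** Suppose R = 5, d = 1.3, the reference is 0.033 and DSX reads 0.044. If the tissue takes the cap shape, DSX is right and the whole 0.011 is model error. If it takes the cone shape, the whole 0.011 is DSX error. The direct comparison gives the same number in both cases.

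**The case against.** The best defence is that the plan foresees the problem. The sentences after the direct comparison introduce a finite element analysis to account for asymmetry, which is a planned estimate of part of the model error. The model's inputs are measured: displacement is controlled, and displacement and force are recorded in synchrony with DSX. The section says the rig applies displacements in order to validate the DSX measurements, and it does not say that actuator displacement is excluded as a reference. If the finite element and mechanical strains are compared at the marker locations, a finite element versus DSX difference follows by subtraction. A condensed article may also leave the formula and the agreement criterion to the full protocol.

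Much of this stands. It defeats the stronger reading that the comparison says nothing about DSX accuracy, because agreement within an estimated model error is partial evidence. There is also no contradiction with the Background sentence on heterogeneous skin. That sentence concerns whole-limb analysis, and the validation section concedes asymmetry itself.

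What does not fall is the structure of the comparison. The article does state which strain is compared directly with DSX and what the finite element result is compared with. As stated, neither comparison isolates DSX error. The point concerns what the text fixes, not a detail left out.

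**Conclusion.** The point holds in a limited form. The reference strain is calculated under a symmetric, circular assumption, and the finite element strain is not stated to be compared with DSX. The direct comparison therefore does not separate DSX error from reference-model error. The actual size of the model error cannot be derived from the article. The one-third figure shows sensitivity to shape under an assumed radius and illustrative shapes, and it is not an estimate of bias.

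A reader might infer that the choice of model outweighs the strain effect the trial is powered for, 0.75 × 0.02 = 0.015 (Power Analysis and Table 1). The documents do not support this. The 0.015 is in vivo shear strain, and the article measures shear as a change in angle between lines, whereas the illustration gives mean radial stretch. At 6 cm the differences are 0.008 and 0.0149, so neither exceeds 0.015.

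Nor does the point reach the clinical comparison directly. The bench model is not used to compute participants' strain. Elevated vacuum and suction are compared within participants by one method, so a constant measurement bias would cancel in the difference. What is limited is the interpretation of the bench validation, and so of Aim 1's accuracy claim for tissue deformation.

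**What to change.** In Validation of DSX Strain Measurements, keep the calculated-strain comparison and add two others.

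1. **Displacement check.** Compare, frame by frame, the DSX-derived axial displacement of markers at the loading contact with the synchronised actuator displacement. Because the fixtures are radiolucent and a tissue marker need not move exactly with the actuator, put a radiopaque marker on the fixture if needed. Report bias and RMS error for all 5 samples. Propagate the error to strain and to angle over the marker gauge lengths actually used. For example, assume independent end-point errors of SD s mm in each direction. A 10 mm line (the length given for the initial cadaver markers) then has a strain error of about √2·s/10 = 0.14s, and the angle between two such lines has an error of about 2s/10 = 0.2s radians.
2. **Finite element against DSX.** Compare finite element strain directly with DSX strain at the same marker locations and load steps, so that disagreement due to asymmetry can be told from DSX error.

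**Cost:** a few sentences and a little more analysis. Actuator displacement and synchronised images are already planned, and the only possible hardware change is a marker on the fixture. **Limits:** the displacement check verifies marker position mainly along one axis and strain only by propagation, so it supplements the strain comparison and does not replace it. The finite element strain remains a model result that depends on its input material properties.

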
**Figure 4 figure4:**
[figure not shown]
Validation apparatus setup. (A) The mechanical testing system interfaces with the dynamic stereo x-ray system. (B) Full view of the testing setup showing testing inclination. (C) Single static biplanar x-ray images of the skin deflected during compressive testing.

### Clinical Experiment

Upon completion of the cadaver trials, a robust marker set will have been developed to evaluate skin strain and residual tibial movement for human participants as part of the clinical experiments. The residual tibial motion will be compared relative to the prosthetic socket for individuals with transtibial limb loss while separately using 2 suspension methods: EV suspension and traditional suction (EV system not activated). Participants will be assessed while walking at a self-selected speed on a treadmill, at a speed 10% faster, and during a step-down task. These activities were chosen for three distinct reasons: (1) their relevance to normal activities [33], (2) the fact that the forces exerted on the lower limb during stepping and walking can displace the prosthetic socket relative to the residual limb, and (3) these movements are suitable for recording by the DSX system. These 2 common suspension conditions (EV and traditional suction) were chosen because of their clinical relevance and expected measurable differences between these conditions.

### Recruitment and Enrollment

The study sample will consist of 21 individuals with unilateral transtibial limb loss recruited from Veterans Affairs New York Harbor Healthcare System. The inclusion and exclusion criteria are presented in Textbox 1.

Inclusion and exclusion criteria.
**Inclusion criteria**
Veteran, service member, or civilian with unilateral transtibial limb loss of any etiologyAged ≥18 years≥6 months after limb lossCurrent prosthesis users for ≥6 hours per day
**Exclusion criteria**
Inability to tolerate socket suspensionLength of the residual limb prohibits socket fitting, marker placement, or dynamic stereo x-ray data captureMental impairment that impedes study complianceCognitive deficits or mental health problems that would limit the ability to participate fully in the study protocolSkin conditions and those with severe contractures that prevent prior prosthetic wearNeuropathy, uncontrolled diabetes, receiving dialysis, insensate feet, severe phantom pain, a history of severe skin ulcers, or any other significant comorbidity that would interfere with the studySevere circulatory problems including peripheral vascular disease and pitting edemaWomen who are pregnant or who plan to become pregnant during participation in the study

### Ethical Considerations

This study was approved by the Veterans Affairs New York Harbor Healthcare System institutional review board (protocol ID 1655582) and the Rutgers University institutional review board (protocol ID Pro2022001576). All participants will provide informed consent before participating in any study activity. No research data will be acquired until the informed consent form has been signed. The principal investigator or study staff will explain the protocol, and participants will be given adequate time to review and comprehend all information before agreeing to participate in the study. After the informed consent form is signed, the study prosthetist will then screen each participant to confirm all inclusion and exclusion criteria and will inspect the residual limb to ensure that there are no issues that could prevent socket fitting. The appropriate residual limb measurements will be taken, and the residual limb will be cast to prepare for socket fabrication. Each participant’s involvement will last approximately 8 weeks, including 4 weeks for socket fabrication and fitting, a 4-week acclimation period, and a data collection visit for CT scans and DSX testing on both socket suspension conditions. Study participants will be compensated US $50 for each of the socket fitting visits (up to 4 maximum) and US $100 for the 1-day data collection and testing at Rutgers. Compensation will be given in the form of a direct deposit voucher, processed through the Veterans Affairs New York Harbor Healthcare System fiscal department.

To protect the privacy and confidentiality of the human participants, each participant will be given a unique identification number that will be used in all study-related paperwork. The specific code system will not contain any personally identifiable information. All information collected throughout the study will be methodically recorded, handled, and stored to allow for accurate reporting, interpretation, and verification. Veterans Affairs (VA) complies with the requirements of the Health Insurance Portability and Accountability Act of 1996 and its privacy regulations and all applicable laws that protect the privacy of research participants. The principal investigator and study staff will ensure that research records are stored in a manner that protects the confidentiality of human participant information. All electronic data collected will be deidentified and will not contain any Health Insurance Portability and Accountability Act identifiers, and the physical study forms (ie, signed consent forms and data collection forms) will be stored in secured and locked filing cabinets at the on-site office of the principal investigator. Computer files will be secured through password protection. Throughout the study, deidentified data (video data and electronic data) will be shared using VA information security office–approved secured VA computer systems with password protection and firewall. The study materials will be stored in accordance with the VA record control schedule.

